### Participant timeline

The SmartAge trial will involve five phases for each participant: study enrollment, which included screening assessment (V0), a baseline visit (V1), a 12-month intervention period, a post-intervention visit (V2), and a follow-up visit (V3). Trial phases are described below and summarized in Fig. 1.

**Fig. 1 Fig1:**
[figure not shown]
SmartAge study flowchart. Abbreviations: MRI: magnetic resonance imaging; *PET* positron emission tomography, *SCD* subjective cognitive decline

#### Enrollment (V0)

Individuals, who express interest in study participation, will undergo following screening procedure to ensure study eligibility. A standardized pre-screening interview conducted over the phone will be administered to collect information on medical and demographic data, on MRI/PET suitability, and on suitability for muscle biopsy. During this interview, the following questions will be asked to endorse the presence of SCD with associated concerns (worries), similar to previous reports and recommendations [15, 51]. Question 1 will be “Do you feel that your cognitive performance has become worse?” (German: “Haben Sie das Gefühl, dass Ihre geistige Leistungsfähigkeit schlechter geworden ist?”, possible answers: yes/no). In case of a positive answer to question 1, question 2 will be asked: “Since when do you have the feeling that your cognitive performance has gotten worse?” (German: “Seit wann hat sich ihre geistige Leistungsfähigkeit verschlechtert?”). In case the answer to question 2 is at least 6 months, question 3 will be asked: “Are you concerned about this cognitive worsening?” (German: “Bereitet Ihnen diese Verschlechterung Sorgen?”, possible answers: yes/no). In case of a positive answer to question 3, question 4 will be asked: “Would you seek or have you sought medical help due to this cognitive worsening?” (German: “Würden Sie diesbezüglich einen Arzt aufsuchen bzw. haben Sie dies bereits getan?”, possible answers: yes/no). Affirmative responses to diagnostic questions 1, 3, 4, and a duration of SCD for at least 6 months are mandatory for study inclusion.

Potential participants that meet inclusion criteria as evaluated during pre-screening will be invited for the on-site screening visit to the Charité – Universitätsmedizin Berlin. Each individual will receive a standardized screening assessment, including neuropsychological tests and questionnaires, to certify the absence of objective cognitive impairment and current psychiatric disorder (e.g., depression). Following measures will be used: (a) Mini-Mental State Examination (MMSE) [52] score ≥ 26, (b) performance above − 1.5 standard deviation (SD) of age-adjusted norms in the Logical Memory II subscale total delayed recall (Story A and B) [53], and the Trail Making Test (TMT) A [54], (c) no deficits on selected items of the Instrumental Activities of Daily Living Scale (IADL) [55], and (d) a Geriatric Depression Scale (GDS) [56] score ≤ 10. After successful completion of the on-site screening assessment, eligible participants will proceed to baseline assessment.

#### Baseline visit (V1)

The baseline visit will encompass a maximum of 4 days with different assessments conducted on each day. On day 1 (carried out immediately after screening, duration: approx. 5 h with breaks), each participant will receive a standardized medical examination that includes fasting blood sampling and physical assessments. Next, a standardized neuropsychological test battery and a questionnaire battery will be administered (Table 1). On day 2, each participant will undergo the MRI assessment (duration: approx. 2 h). On day 3, muscle tissue biopsy will be carried out to determine autophagy signaling (optional consent, duration: approx. 2–3 h, aiming for 25 participants). On day 4, a cerebral Aβ PET assessment is performed (optional consent, baseline visit only, duration: approx. 2–3 h, aiming for 50 participants). After completion of the baseline visit, participants will be randomly assigned to one intervention arm. The Aβ PET measurements will in most cases be conducted after intervention has started, due to logistic reasons.

#### Intervention period

During the intervention, at 3 months, 6 months, and 9 months after the baseline visit (V1), telephone or on-site interviews will be scheduled with each participant to obtain information on participants’ physical and mental well-being, trial compliance, changes in dietary habits, and current medication intake. The study assessor will also ask for possible adverse events (AEs) and serious adverse events (SAEs). At 6 months after baseline, the remaining capsules will be counted to monitor adherence to capsule intake and new capsules for the next 6 months will be provided. Moreover, participants will be asked for their subjective estimation of compliance to intervention. At the post-intervention visit (V2), capsule counting procedures and subjective estimation of compliance will be repeated.

#### Post-intervention visit (V2)

The post-invention visit will take place at the end of the 12-month intervention period. Assessments of the post-intervention visit will be conducted on a maximum of 3 days, to be scheduled in close temporal proximity. On day 1, the standardized screening assessment (see Table 1) is re-administered to determine possible changes in the SCD diagnostic criteria, followed by the same assessments as for the baseline visit, that is, the standardized medical examination, the standardized neuropsychological test battery and questionnaire battery. In addition, participants will be asked to provide qualitative feedback on the intervention. On day 2, the MRI assessment will be carried out and on day 3, the muscle tissue biopsy will be obtained (optional consent).

#### Follow-up visit (V3)

The follow-up visit will take place 18 months after baseline visit. The visit will include following assessments: standardized screening assessment, standardized medical examination without blood draw, and adapted versions of the standardized neuropsychological test battery and questionnaire battery (see Table 1). The participants will be asked to provide qualitative feedback on the intervention.

### Sample size

A power calculation was conducted to estimate the number of participants required to detect a group difference in the primary outcome (i.e., mnemonic discrimination performance) at the end of the intervention. Sample size estimation was based on behavioral data obtained in a phase IIa pilot trial [37]. In this pre-study on 30 SCD participants (dropout: *n* = 2) and a 3-month intervention period, we determined an effect size of Cohen’s *d* = 0.65 on the group difference in change of mnemonic discrimination performance between baseline (V1) and the end of intervention (V2). Since this is a first estimate of the effect size based on a small sample, we based our sample size estimation for the present phase IIb trial on a smaller effect size of Cohen’s *d* = 0.5. To demonstrate a significant effect in the primary outcome, 50 participants per group (including a 10% dropout rate) need to be incorporated in the analysis with an unpaired-sample *t* test (two-sided significance level = 0.05, power 80%). Sample size estimation was conducted using a conservative approach [57] based on an unpaired-sample *t* test, even though the intended analysis of the primary outcome will be performed using analysis of covariance (ANCOVA) models. Case number estimation was compiled with the R package “pwr” [58].

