**Methods:**

The SmartAge trial is a monocentric, randomized, double-blind, placebo-controlled phase IIb trial. The study will investigate 12 months of intervention with spermidine-based nutritional supplementation (target intervention) compared with 12 months of placebo intake (control intervention). We plan to recruit 100 cognitively normal older individuals with SCD from memory clinics, neurologists and general practitioners in private practice, and the general population. Participants will be allocated to one of the two study arms using blockwise randomization stratified by age and sex with a 1:1 allocation ratio. The primary outcome is the change in memory performance between baseline and post-intervention visits (12 months after baseline). Secondary outcomes include the change in memory performance from baseline to follow-up assessment (18 months after baseline), as well as changes in neurocognitive, behavioral, and physiological parameters (including blood and neuroimaging biomarkers), assessed at baseline and post-intervention.

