## Methods: participants, intervention, and outcomes

### Trial design and setting

This is a monocentric, randomized, double-blind, placebo-controlled phase IIb trial, carried out at the NeuroCure Clinical Research Center, Charité – Universitätsmedizin Berlin.

The trial includes 12 months of intervention with spermidine supplementation (target intervention) compared with 12 months of placebo intake (control intervention). The trial will compare outcomes of the two intervention groups, with participants randomized to one of the two study arms. Randomization is performed blockwise with a 1:1 allocation ratio. The SmartAge trial has been approved by the responsible Institutional Review Board and will be carried out in compliance with institutional ethical standards and the Declaration of Helsinki.

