### Adverse events monitoring and reporting

The occurrence of AEs and SAEs will be constantly monitored throughout the SmartAge trial. Participants will be instructed to immediately contact the research team in case of any self-noticed health changes or unexpected medical care visits. In addition, participants will receive a study pass, which informs about participation in the SmartAge trial and provides contact information in case of an SAE/hospitalization. All AEs and SAEs will be reported to and documented by the responsible study physician (SAEs within 24 h).

In general, the risk of health damage due to spermidine supplementation can be expected to be minimal, based on a prior interventional report [35] and our safety study [36]. Participants will be informed about all possible risks and can withdraw consent at any time without providing reasons. The expected “dropout” rate will be balanced in advance by the number of participants.

In case an SAE occurs, the study physician will first make an assessment as to whether or not a causal relationship with the intake of the investigational supplement is considered possible. Since this is a double-blinded trial, the assessment will be done without knowledge of group affiliation (spermidine and placebo). Emergency unblinding is possible, if the decision on follow-up medical treatment may depend on the participant’s allocated intervention during the trial. If more than three of the enrolled participants suffer from SAEs that are likely to be associated with spermidine intake (as assessed by the study physician), the SmartAge trial will be discontinued. All SAEs (whether or not related to the intervention) and all relevant pseudonymized documentation related to the SAE will be documented in the SAE report form, dated and signed by the principal investigator and included in the CRF documentation.

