### Statistical methods

Statistical analyses of the primary outcome and secondary outcomes will be specified in the statistical analysis plan, to be written and registered before breaking the blind of study investigators. Statistical analyses of the primary outcome will be conducted by a designated statistician. Statistical analyses of secondary outcomes and additional exploratory analyses will be carried out by study investigators.

The primary outcome will be analyzed using an “intention to treat” (ITT) approach, consisting of all participants randomized into the trial, regardless of length of intervention. Subsequently, a “per protocol” analysis is carried out, including only those participants, who finished the 12-month intervention period. We will assess the between-group difference in the change of memory performance, operationalized by mnemonic discrimination performance, between baseline (V1) and the end of intervention (V2). Statistical analysis will be performed using an ANCOVA model with the change in memory performance (V2–V1) as dependent variable, intervention group as independent variable, and baseline memory performance as well as age as co-variates. Analyses of secondary endpoints will be conducted using comparable statistical methods. For example, analysis of change in memory performance between baseline (V1) and follow-up assessment (V3) will be carried out by means of ANCOVA. In this model, change in memory performance (V3–V1) will represent the dependent variable, with intervention group as the independent variable and baseline scores and age inserted as covariate.

In case of missing primary endpoints, the primary analysis will be done by using multiple imputation methods. It will further be investigated whether demographic or biological factors are associated with primary and secondary endpoints and / or modulate the response to the intervention, by integrating these variables into statistical models as covariates (or as interactive term with the intervention group). The main hypothesis is tested at a two-sided significance level of alpha = 0.05, using the ITT data set with multiple imputation.

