Other limitations of this phase IIb trial include the time period of intervention, which is still relatively short given the slow evolution of AD pathogenic processes in non-demented older individuals [83], and the restricted number of participants. Larger multi-center phase III trials with 1000–2000 participants and trial durations of 1.5–2 years commonly select clinical outcome measures, which are however less sensitive [84]. We deliberately chose a highly sensitive performance-based outcome measure, given our relatively short intervention time and manageable number of subjects. Although we recognize the importance of larger sample sizes, we remain optimistic that any subtle cognitive changes in our at-risk population will be detected based on our previous phase IIa trial [37]. Lastly, it is important to highlight that a multi-center trial implementation was not financially attainable. Pending the positive results of this trial, public funding for a phase III trial will be applied for, to move this intervention into clinical routine.

Overall, the SmartAge trial aims to contribute to the establishment of an effective and well-tolerable nutrition intervention to promote brain and cognitive health in older individuals at higher risk of dementia. A positive outcome with regard to memory performance in the spermidine-treated group may initiate a large multi-center phase III trial with a profound impact on public health, patients with SCD, and their families.

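### Fifty participants per group do not give the stated 80% power: the protocol's own t-test inputs need 64 evaluable per group, and 45 to 50 give 65% to 70%

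*Protocol article*

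**What the plan says.** The Sample size section gives every input. The pilot estimate was d = 0.65 for the group difference in change between V1 and V2. Because that came from a small sample, the calculation was based "on a smaller effect size of Cohen’s *d* = 0.5". The test and target are given as "two-sided significance level = 0.05, power 80"%, and the conclusion is that "50 participants per group (including a 10% dropout rate) need to be incorporated in the analysis with an unpaired-sample" t test. The software named is the R package pwr.

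The same section calls the t-test calculation conservative, since the primary analysis will be ANCOVA. No baseline-to-12-month correlation or explained variance is given there or elsewhere in the article.

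Other sections agree on the framework. The abstract says "We plan to recruit 100 cognitively normal older individuals with SCD". Trial design and setting says "Randomization is performed blockwise with a 1:1 allocation ratio". Statistical methods says "The main hypothesis is tested at a two-sided significance level of alpha = 0.05", with ANCOVA of the V2–V1 change adjusted for baseline memory performance and age, in the intention-to-treat set with multiple imputation.

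**The concern.** A two-sided t test at d = 0.5 with 80% power is a familiar case that needs a little over 60 per group before any dropout allowance. A total of 50 per group with dropout already included is well short of that.

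The calculation is the only justification given for N = 100 on the primary endpoint. If it is wrong, the stated 20% risk of missing the planned effect is wrong on the basis used to derive it. The deliberate step down from the pilot's 0.65 to 0.5 also loses much of its purpose, because the effect the t test can detect with 80% power moves back up towards the pilot value.

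**Working it through.** **Inputs**, all from the Sample size section: d = 0.5 (standardised, so no SD is needed); unpaired t test; two-sided alpha 0.05; power 80%; dropout 10%; 50 per group. Equal allocation and the two-sided test are confirmed in Trial design and setting and in Statistical methods.

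**Step 1. Try to reproduce 50 per group.**

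- Normal approximation: n = 2(1.960 + 0.842)² / 0.5² = 2 × 7.85 / 0.25 = 62.8, so 63 per group.
- Noncentral t, which is the calculation pwr performs: n = 63.77, so 64 per group.
- With 10% dropout: 63.77 / 0.9 = 70.9, or 64 / 0.9 = 71.1, so 71 to 72 randomised per group (142 to 144 in total).

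The stated figure is not reproduced. It is below even the requirement with no dropout, which is 2 × 64 = 128 in total.

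**Step 2. Power of the stated design by t test.** The noncentrality is d × √(n/2), with 2n − 2 degrees of freedom.

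| Reading of the sentence | Evaluable per group | Noncentrality | Power at d = 0.5 | d detectable with 80% power |
|---|---|---|---|---|
| 50 randomised, 10% lost | 45 | 0.5 × √22.5 = 2.37 | 65.0% | 0.60 |
| 50 analysed | 50 | 0.5 × √25 = 2.50 | 69.7% | 0.57 |

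The normal approximation gives 66.0% and 70.5%, so the result does not depend on the method.

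**Step 3. What would give 50?** Two changed inputs do:

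- One-sided alpha 0.05 at d = 0.5 with no dropout allowance: n = 50.15.
- Two-sided alpha 0.05 at d = 0.6: n = 44.6, so 45, and 45 / 0.9 = 50.

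Each contradicts the text. They are possible explanations of the slip, and the document supports neither over the other.

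**Step 4. What the planned ANCOVA could add.** Take d on the SD of the change score, as the pilot effect is described, with equal variances at V1 and V2 and no gain from age. With correlation ρ between baseline and 12 months, the change-score variance is proportional to 2(1 − ρ) and the ANCOVA residual variance to 1 − ρ². Their ratio is (1 + ρ)/2, so the effective d is 0.5 / √((1 + ρ)/2).

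| Assumed ρ | Effective d | Power, 45 per group | Power, 50 per group |
|---|---|---|---|
| 0.3 | 0.62 | 83% | 87% |
| 0.4 | 0.60 | 80% | 84% |
| 0.5 | 0.58 | 77% | 82% |
| 0.6 | 0.56 | 75% | 79% |
| 0.7 | 0.54 | 72% | 77% |
| 0.8 | 0.53 | 70% | 74% |

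Put another way, the covariates must explain about 30% of the change-score variance with 45 per group, or about 22% with 50, to restore 80%. Setting (1 + ρ)/2 equal to 0.70 and 0.78 gives ρ of about 0.40 and 0.56 as the upper limits under these assumptions.

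**The case against.** The strongest reply is that the t test is not the planned analysis. ANCOVA with baseline and age is, and sizing on a t test while analysing by ANCOVA is normally a safe choice. This is right in part. A reader might infer from Step 2 that the trial itself has 65% power, and the document does not support that: 65% is the t-test figure under one reading of the sentence, and the ANCOVA range includes values above 80%. But the section attributes 80% to the t test, and the t test does not deliver it. Sizing on a t test is conservative only if N meets the t-test requirement, and here it does not.

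The ANCOVA figures are also not firm limits. If the SD at V2 were 0.9 of that at V1, power with 45 per group at ρ = 0.5 would be 82%. If it were 1.1 times, power at ρ = 0.4 would be 77%. Age might add a little. The document gives none of these quantities, so it neither establishes 80% nor rules it out.

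A second reply is that the sentence can mean 50 analysed, and that multiple imputation keeps all 100 in the analysis set. The first reading stands as possible and gives 70%. Imputation keeps participants in the data set but does not generally restore the information lost with missing endpoints.

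Three further inferences are tempting and should not be drawn:

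- **Higher dropout.** The pilot lost 2 of 30 in 3 months, but two events are too few to extrapolate to 12 months. The 10% is a planning choice that nothing in the document contradicts, and "The expected “dropout” rate will be balanced in advance by the number of participants" only restates that an allowance was made.
- **A promise of detection.** In the Discussion, "we remain optimistic that any subtle cognitive changes in our at-risk population will be detected based on our previous phase IIa trial" is an opinion within a limitations paragraph that itself names the small number of participants.
- **Misreading of a null result.** No section plans to treat a non-significant result as evidence of no effect.

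**Conclusion.** The sample size statement is wrong as written. Its inputs require 64 evaluable per group (71 to 72 randomised), against the stated 50. On the stated t-test basis power is 65% with 45 evaluable or 70% with 50 analysed, a shortfall of 15 or 10 percentage points, and the effect detectable with 80% power is d = 0.60 or 0.57 instead of 0.5. This part needs no assumption beyond the document's own figures.

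Whether the planned ANCOVA reaches 80% is open: about 70% to 83% with 45 per group and 74% to 87% with 50, for correlations from 0.8 down to 0.3. That part rests on d being defined on the change-score SD, equal variances, no gain from age, and a correlation that the document does not state. The finding is an incorrect power claim for the primary endpoint. It does not show that the trial is underpowered under its planned analysis.

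**What to change.** Keep N = 100 and correct the Sample size section:

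1. Say whether 50 per group are randomised (45 evaluable) or 50 are evaluable.
2. Replace the 80% claim with the matching t-test statement: 45 evaluable per group give 65% power for d = 0.5 and 80% power for d = 0.60; or 50 evaluable give 70% and d = 0.57 (unpaired t test, two-sided 0.05).
3. Stop calling the t-test basis conservative in support of this N.
4. If 80% is to rest on ANCOVA, state the assumed baseline-to-12-month correlation and its source, for example the pilot data, and show power over a range such as 0.3 to 0.8.
5. If a different alpha or effect size was actually entered in the software, state it and reconcile it with the text.

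The cost is a wording change and possibly one correlation from the pilot data. No participants, visits or analyses are added. The price is a less favourable power figure on the t-test basis.

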### Recruitment

Study participants will be recruited from memory clinics, neurologists, and general practitioners in private practice in Berlin and from the general population in Germany through advertisements.

## Methods: assignment of intervention

### Allocation

Participants will be randomly assigned to the spermidine or the placebo group. A blockwise (block size of 6) randomization sequence, stratified by age (60–70, 70–80, and 80–90 years) and sex, will be generated using a computer-based algorithm (http://www.randomization.com/). Participant allocation will be performed at a 1:1 ratio by a study investigator without involvement in outcome assessments.

